# Table 9. The effect of HIV infection on 2-month sputum culture conversion

*2-month culture conversion rate*

| *Study* | *HIV-positive* | *HIV-negative* |
| --- | --- | --- |
| Study 22 (TBTC, unpublished data) | 90.4% (47/52) | 79.4% (682/865) |
| Zaire [43] | 92.9% (223/240) | 92.1% (164/178) |
| Sterling (time to culture conversion) [44] | 77 days | 72 days |

INH resistance

Mycobacterial culture and drug susceptibility testing can require up to 8 weeks. Therefore, patients having drug-resistant isolates are likely to be enrolled in this trial and treated for most of the intensive phase of therapy prior to the receipt of the drug-susceptibility test results. The most common form of drug resistance in the United States, Canada, and Uganda is INH-resistance, with rates of 5-10% among patients without prior tuberculosis treatment. INH-resistance does not appear to have a substantial impact on sputum culture conversion (Table 10). However, INH-resistance appears to be associated with slightly higher rates of treatment failure and relapse, raising the possibility that absence of difference in 2-month sputum culture conversion rates may not indicate equivalence. In addition, current TB treatment guidelines suggest use of rifampin, pyrazinamide, plus ethambutol for individuals with INH-resistant isolates. Therefore, patients with INH-resistant isolates will be taken off of their assigned study regimen and treated using an individualized regimen at the discretion of the principal investigator. These patients will not be included in the analysis of sputum culture conversion.

**Table 10.** Effect of initial resistance to INH on outcomes of TB treatment [45]

| Outcome | INH-resistance | Drug-susceptible |
| --- | --- | --- |
| 2-month sputum culture conversion | 88% (132 / 150) | 89% (1123 / 1262) |
| Treatment failure | 0.6% (1 / 172) | 0.1% (2 / 3177) |
| Relapse | 9.0% (13 / 149) | 4.0% (123 / 2954) |

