Study entry is open to male and female patients and patients of all ethnic backgrounds.  Historically, the majority of patients with tuberculosis at clinical sites are males.  The gender, ethnic and socioeconomic background of the subjects recruited for this study is expected to mirror that of the population the hospitals and clinics served, and that of the population most affected by tuberculosis. Pregnant or breast-feeding women and children will not be enrolled because of uncertainties about the safety of moxifloxacin in those groups of patients.  Subjects will be enrolled if they meet all of the following inclusion criteria and none of the exclusion criteria:

- - 1. Inclusion Criteria

1. Suspected pulmonary tuberculosis with acid-fast bacilli in a stained smear of expectorated or induced sputum. Patients whose sputum cultures do not grow *M. tuberculosis* and those having an *M. tuberculosis* isolate resistant to (one or more) isoniazid, rifampin, pyrazinamide, or fluoroquinolones will be discontinued from the study, but followed for 14 days to detect late toxicities from study therapy. Patients having extra-pulmonary manifestations of tuberculosis, in addition to smear-positive pulmonary disease, are eligible for enrollment. Sputum must be expectorated or induced; smear results from respiratory secretions obtained by bronchoalveolar lavage or bronchial wash may not be used for assessment of study eligibility.
2. Willingness to have HIV testing performed, if HIV serostatus is not known or if the last documented negative HIV test was more than 6 months prior to enrollment. HIV testing does not need to be repeated if there is written documentation of a positive test (positive ELISA and Western Blot or a plasma HIV-RNA level greater than 5000 copies/ml) at any time in the past
3. 7 (seven) or fewer days of multidrug therapy for tuberculosis disease in the 6 months preceding enrollment
4. 7 (seven) or fewer days of fluoroquinolone therapy in the 3 months preceding enrollment
5. Age > 18 years
6. Karnofsky score of at least 60 (requires occasional assistance but is able to care for most of his/her needs; see Appendix B)
7. Signed informed consent
8. Women with child-bearing potential must agree to practice an adequate (barrier) method of birth control or to abstain from heterosexual intercourse during study therapy.
9. Laboratory parameters done at, or  14 days prior to, screening:

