All baseline isolates of *Mycobacterium tuberculosis* will undergo drug susceptibility testing at the site’s local laboratory. The baseline isolate will be defined as the first *M. tuberculosis* isolate obtained from a sputum culture; in some instances this sputum specimen may have been obtained prior to study screening. An *M. tuberculosis* isolate cultured in a laboratory other than a site’s study laboratory of record may be designated as the baseline isolate if the isolate is sent to the study laboratory of record. Drug susceptibility testing will include susceptibility to isoniazid, rifampin, and ethambutol. Initial susceptibility testing generally requires 4-8 weeks to complete (initial isolation followed by susceptibility testing). It is expected that patients will be enrolled in this protocol with drug-resistant isolates, most often resistance to isoniazid, with or without streptomycin resistance[109, 110]. Rifampin resistance and multidrug-resistance (resistance to isoniazid and rifampin) is uncommon among previously untreated patients in the United States[109], Uganda[110], Canada[111], and South Africa[112]. All isolates will be sent to the CDC Mycobacteriology Laboratory for confirmatory susceptibility testing; this testing will include all drugs currently used to treat tuberculosis, including pyrazinamide and fluoroquinolones. The confirmatory testing will take several additional months, and these results are unlikely to be available during the first 2 months of TB treatment. All study regimens should be highly active for isolates with susceptibility to isoniazid and rifampin.

- 1. Management of patients with baseline drug-resistant isolates

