Isoniazid resistance – Isoniazid resistance does not appear to affect sputum culture conversion, but is associated with slightly higher rates of treatment failure and relapse (Introduction, “Factors other than therapeutic regimen known to affect 2-month culture-conversion”), and current guidelines suggest the use of rifampin, pyrazinamide, and ethambutol for patients with isoniazid-resistant isolates. Patients with isoniazid resistance will be taken off of their assigned study regimen and treated using an individualized regimen at the discretion of the principal investigator. These patients will not be included in the analysis of sputum culture conversion. Patients receiving study (intensive) phase therapy at the time of discontinuation of the study regimen will have a study visit at 2 weeks after discontinuation of the study regimen for assessment of delayed toxicity, and then will no longer be followed in the study. Patients receiving continuation phase therapy at the time of discontinuation will no longer be followed in the study.

Fluoroquinolone resistance – Rates of fluoroquinolone resistance are extremely low in the United States and Canada (0.3% among rifampin-susceptible isolates) [10]and likely to be very low in Africa. Patients having a fluoroquinolone resistant isolate will be taken off their assigned study regimen and treated using an individualized regimen at the discretion of the investigator. These patients will not be included in the analysis of sputum culture conversion. Patients receiving study (intensive) phase therapy at the time of discontinuation of the study regimen will have a study visit at 2 weeks after discontinuation of the study regimen for assessment of delayed toxicity, and then will no longer be followed in the study. Patients receiving continuation phase therapy at the time of discontinuation of the study regimen will no longer be followed in the study.

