Resistance to two or more drugs - Patients with resistance to any two or more of the study drugs, most likely isoniazid and ethambutol or pyrazinamide, will be taken off their assigned study regimen and treated with an individualized regimen at the discretion of the investigator. These patients will not be included in the analysis of sputum culture conversion. Patients receiving study (intensive) phase therapy at the time of discontinuation of the study regimen will have a study visit at 2 weeks after discontinuation of the study regimen for assessment of delayed toxicity, and then will no longer be followed in the study. Patients receiving continuation phase therapy at the time of discontinuation will no longer be followed in the study.

Resistance to a non-study drug, with or without isoniazid-resistance – Rates of resistance to streptomycin are relatively high (7-10%) and often associated with isoniazid-resistance. In that resistance to non-study drugs should not affect the activity of the study drugs, patients with isolates having resistance to non-study drugs will be kept on their assigned study regimen and included in the analysis of sputum culture conversion.

- 1. Study drug toxicity

Patients will be closely monitored for signs and symptoms of study drug toxicity. For all toxicities that are treatment-emergent and that require the study therapy to be temporarily or permanently discontinued, relevant clinical and laboratory tests will be obtained as clinically indicated and repeated as needed until final resolution or stabilization of the toxicity.

If a patient develops hepatic toxicity requiring study drug discontinuation, the following evaluation will be undertaken: assessment for history of injection or noninjection drug use, alcohol ingestion, use of other hepatotoxic drugs, and performance of serologic tests for viral hepatitis (IgM antibody for Hepatitis A, Hepatitis B surface antigen, IgM antibody to Hepatitis B core antigen, antibody to Hepatitis C).

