All symptoms and laboratory findings will be graded according to severity using the modified National Cancer Institute Common Toxicity Criteria (Appendix E). For the purposes of this study, pregnancy will be reported on the Adverse Event Form. All pregnant patients will be taken off study therapy and treated using the ATS/IDSA/CDC guidelines for tuberculosis treatment during pregnancy. Women who become pregnant will continue to receive scheduled follow-up, not receive additional x-rays unless clinically indicated, and be classified as being on a non-study regimen. The outcome of the pregnancy will be reported on the Adverse Event Follow-up Form.

- 1. Adverse event reporting

An adverse experience is defined as any unintended or abnormal clinical observation that is not of benefit to the patient. The adverse experiences that must be reported on an Adverse Event Form include: pregnancy, new medical diagnosis, grade 3 or 4 toxicity (potentially medication-related or other causes), study drug discontinuation, medication side-effects that are grade 3 or 4, and serious adverse events (defined in next paragraph). At the time of enrollment, if the patient already has a medical diagnosis whose signs or symptoms worsen during the study to a Grade 3 or 4, this is an adverse event that must be reported.

A serious adverse event (SAE) is defined as any experience that is fatal or life-threatening, is persistently or significantly disabling (as determined by the principal investigator), requires inpatient hospitalization, or prolongation of hospitalization, is a congenital anomaly, or overdose of study drugs. Any Grade 4 toxicity is considered an SAE.

The study drugs are moxifloxacin, ethambutol, isoniazid, rifampin, and pyrazinamide. The most common adverse effects associated with the study drugs are specified in Section 2.2 - "Study Drugs". The investigator is responsible for monitoring all adverse events that are observed or reported during the study, regardless of whether they are related to study drugs.

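### Section 5.2 keeps isolates resistant to isoniazid plus a non-study drug on regimen and in the conversion analysis, against the isoniazid rule stated everywhere else in the protocol

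*Protocol*

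**What the plan says.** The closing resistance paragraph of Protocol Section 5.2 carries the heading "Resistance to a non-study drug, with or without isoniazid-resistance". It notes that streptomycin resistance is fairly common (7-10%) and often accompanies isoniazid resistance. It reasons that resistance to drugs outside the regimen should not weaken the study drugs, and concludes that "patients with isolates having resistance to non-study drugs will be kept on their assigned study regimen" and counted in the conversion analysis.

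Elsewhere the rule for isoniazid resistance is the opposite:

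- **Section 5.2, isoniazid paragraph:** "Patients with isoniazid resistance will be taken off of their assigned study regimen". They are also left out of the conversion analysis, and follow-up ends (after a two-week toxicity visit if they were still in the intensive phase).
- **Introduction, INH resistance:** "patients with INH-resistant isolates will be taken off of their assigned study regimen", and again they are not analysed for conversion.
- **Inclusion criterion 1 (synopsis and Section 3.8.1):** a patient with an "isolate resistant to (one or more) isoniazid, rifampin, pyrazinamide, or fluoroquinolones will be discontinued from the study".
- **Section 6.1, fifth exclusion:** a baseline isolate resistant to isoniazid removes the patient from the conversion analysis.

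Section 5.4 settles which drugs count as study drugs: "The study drugs are moxifloxacin, ethambutol, isoniazid, rifampin, and pyrazinamide". Streptomycin is not among them.

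**The concern.** A patient whose isolate resists both isoniazid and streptomycin falls under two rules with opposite outcomes. Section 5.1 expects such patients: it says the resistant isolates enrolled will show "most often resistance to isoniazid, with or without streptomycin resistance".

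Four things are at stake.

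1. **Treatment.** The isoniazid paragraph cites guidelines that favour rifampin, pyrazinamide and ethambutol for these isolates. The closing paragraph tells the site to carry on with the assigned regimen. A patient who stays on study then moves towards the Section 3.2 continuation regimens. These are built on isoniazid plus a rifamycin, and the one isoniazid-free option is listed for intolerance.
2. **Handling that depends on the local laboratory.** The required local panel omits streptomycin: "Drug susceptibility testing will include susceptibility to isoniazid, rifampin, and ethambutol". A site running only that panel applies the isoniazid paragraph. A site that also tests streptomycin meets the heading of the closing paragraph.
3. **Membership of the primary analysis.** Section 6.1 excludes these patients and Section 5.2 includes them.
4. **Follow-up.** One rule ends follow-up. The other keeps the patient on study, where he or she can contribute to the secondary comparison of treatment failure after 4 months.

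**Working it through.** **Do the rules really collide?** For an isolate resistant to isoniazid and streptomycin:

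| Source | Regimen or study status | Conversion analysis | Follow-up |
| --- | --- | --- | --- |
| 5.2, non-study-drug paragraph | stays on regimen | included | continues (implied) |
| 5.2, isoniazid paragraph | off regimen | excluded | ends |
| Introduction, INH resistance | off regimen | excluded | not addressed |
| Inclusion criterion 1 | discontinued from the study | not addressed | 14 days |
| 6.1, fifth exclusion | not addressed | excluded | not addressed |

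The paragraph on resistance to two or more drugs does not break the tie. It counts study drugs, and this isolate resists only one. The rationale in the closing paragraph does not help either, because it speaks of non-study drugs and isoniazid is a study drug.

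**How many patients?** Inputs: 410 patients (Section 3.7), isoniazid resistance 5-10% (Introduction), streptomycin resistance 7-10% (Section 5.2). The joint rate is not given, so I bound it.

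- Isoniazid-resistant in total: 410 × 0.05 = 20.5; 410 × 0.10 = 41.
- Both, if independent: 410 × 0.05 × 0.07 = 1.4; 410 × 0.10 × 0.10 = 4.1.
- Both, at full overlap: 410 × min(0.05, 0.07) = 20.5; 410 × min(0.10, 0.10) = 41.

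Since the protocol calls the two resistances often associated, the independence figure is likely too low.

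**Effect on the conversion rate.** Table 10 gives 2-month conversion by isoniazid resistance.

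- Resistant: 132/150 = 0.8800. Susceptible: 1123/1262 = 0.8899. Difference −0.0099.
- SE = √(0.8800 × 0.1200/150 + 0.8899 × 0.1101/1262) = 0.0280.
- 95% CI: −0.0647 to +0.0449.

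If a fraction f of the analysed control arm is isoniazid-resistant, its rate moves by f × (difference). Taking f among those analysed as equal to f among those enrolled:

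- Smallest: 0.0035 × 0.99 = 0.003 points lower.
- Full overlap at 10%: 0.10 × 0.99 = 0.10 points lower.
- Full overlap at the lower confidence limit: 0.10 × 6.47 = 0.65 points lower.

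The shift is placed in the control arm because only that arm receives isoniazid in the intensive phase. The design difference is 88 − 75 = 13 points.

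**Sample size.** The stated 154 per group reproduces with the continuity-corrected two-proportion formula (75% vs 88%, two-sided 0.05, 80% power). Without the correction the formula gives 139. Then 154/(1 − 0.25) = 205.3, matching the stated 205 per arm. The 25% allowance explicitly covers drug resistance, so excluding these patients costs nothing beyond what is already planned.

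**The case against.** The strongest reply is that this is a stray phrase in one heading. The operative sentence speaks only of resistance to non-study drugs, its rationale goes no further, and every other statement of the isoniazid rule agrees. Section 6.1 alone defines the conversion analysis set, and it is unambiguous. The local-panel point is limited because all isolates go to the central laboratory for testing against all drugs in current use, so final classification for analysis need not depend on local streptomycin testing. Both arms already contain rifampin, pyrazinamide and ethambutol, and local results generally take 4-8 weeks, so any extra time on the assigned intensive regimen is usually short. The numerical effect is negligible.

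Much of this stands. Section 6.1 is clear by itself, the effect on the estimate is tiny, and central testing can settle the analysis set.

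Three points do not yield:

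- The phrase cannot be read as idle. The rifampin paragraph of Section 5.2 uses the same with-or-without form in its heading to bring co-resistant isolates under its rule, and the closing paragraph itself goes on to mention the link between streptomycin and isoniazid resistance.
- Central results take several further months (Section 5.1), too late to guide the site's treatment decision.
- The intensive phase is not the whole exposure. Retention leads towards isoniazid-based continuation therapy. In Table 10, relapse was 13/149 (8.7%, printed as 9.0%) with isoniazid resistance and 123/2954 (4.2%, printed as 4.0%) in drug-susceptible disease.

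**Conclusion.** The concern holds. As written, Section 5.2 gives two incompatible instructions for isolates resistant to isoniazid and a non-study drug, and one of them contradicts inclusion criterion 1, the Introduction and Section 6.1. The consequence is chiefly for treatment and follow-up at the sites, and secondarily for consistency about who is in the primary analysis. This is not a finding of material bias or lost power.

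The size rests on three assumptions: the unknown overlap, bounded here by independence and full overlap; the Table 10 difference applying to this control regimen; and streptomycin resistance adding no effect of its own, since streptomycin is not given.

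**What to change.** In the closing resistance paragraph of Section 5.2, delete the reference to isoniazid resistance from the heading and limit the paragraph to isolates susceptible to isoniazid, rifampin, pyrazinamide and fluoroquinolones. The isoniazid paragraph and Section 6.1 then govern every isoniazid-resistant baseline isolate in both arms, whatever else it resists. Ethambutol is deliberately left off the list, so that the existing rule keeping ethambutol-resistant patients on regimen still works.

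Section 6.1 needs no change. The cost is a one-line clarifying amendment and a memo to sites, with no change to sample size or analysis method.

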- Serum amino aspartate transferase (AST) activity ≤ 3 times the upper limit of normal
- Serum total bilirubin level ≤ 2.5 times the upper limit of normal
- Serum creatinine level ≤ 2 times the upper limit of normal
- Complete blood count with hemoglobin level of at least 7.0 g/dL
- Complete blood count with platelet count of at least 50,000/mm3
- Serum potassium ≥ 3.5 meq/L
- Negative pregnancy test (women of childbearing potential)
  - 1. Exclusion Criteria

1. Breast-feeding
2. Known intolerance to any of the study drugs
3. Known allergy to any fluoroquinolone antibiotic
4. Concomitant disorders or conditions for which moxifloxacin (MXF), isoniazid (INH), rifampin (RIF), pyrazinamide (PZA), or ethambutol (EMB) are contraindicated. These include severe hepatic damage, acute liver disease of any cause, and acute uncontrolled gouty arthritis.
5. Current or planned therapy during the intensive phase of therapy using drugs having unacceptable interactions with rifampin (rifabutin can be substituted for rifampin during the continuation phase of therapy)
6. Current or planned antiretroviral therapy during the intensive phase of therapy
7. History of prolonged QT syndrome or current or planned therapy with quinidine, procainamide, amiodarone, sotalol, disopyramide, ziprasidone, or terfenadine during the intensive phase of therapy.
8. Pulmonary silicosis
9. Central nervous system TB
10. **STUDY PLAN**
    1. Study Procedures
       1. Screening Visit

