Patients will have study visits 2, 4, 6, and 8 weeks after enrollment. At each of these study visits heart rate, blood pressure, respiratory rate, temperature, and weight will be measured and a sputum sample will be obtained. If the patient is unable to spontaneously expectorate a sputum sample at any of these times, an attempt will be made to induce sputum production by aerosol inhalation. Study sites will use their local procedure for sputum induction. A sputum sample will be defined as unobtainable (and negative for analytic purposes) if no sputum can be obtained after an attempt at sputum induction. Laboratory tests for toxicity monitoring will also be obtained at study visits during the intensive phase of therapy. These tests will be a complete blood count and serum AST, total bilirubin, and creatinine. Visual acuity and color vision testing, per standard site practice, will be repeated at the 4 week visit. Patients found to have HIV infection, per the result of testing done at screening, will have blood drawn for a CD4 cell count at the week 2 study visit (or at the first study visit after HIV infection is documented.) Patients with documented HIV infection at screening, for whom written results of CD4 testing done within 6 months prior to the start of study therapy cannot be obtained, will have blood drawn for these tests as part of the study at the week 2 study visit. Participants not in routine HIV care will be referred for such care, particularly if the CD4 count is low (i.e. < 200 cells/mm3). At each study visit during the intensive phase of therapy, patients will be asked about what medications they have been taking and if they have had any illnesses that would qualify as a new diagnosis or adverse event since the last visit.

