In general, for grade 1 toxicities, the patient will be followed carefully and the study drugs will be continued. For grade 2 toxicities, the patient will be followed more carefully, with additional laboratory and/or clinic visits as necessary, and the study drugs temporarily held at the investigator's discretion. For any grade 3 toxicity that, in the principal investigator’s judgment is due to study drug(s), the causative study drug(s) should be held. The clinician should rule out other possible causes of the symptoms before discontinuing study medication. When possible, concomitant medications should be held first at the discretion of the principal investigator if he/she suspects they are contributing to the toxicity. Depending on the nature and severity of the toxicity, the degree to which it resolves, and/or the emergence of alternative explanations for the toxicity or the subject’s deterioration, the study drugs(s) may be restarted at the discretion of the investigator. For any recurring grade 3 or grade 4 toxicity, the study drugs should be temporarily held and may be permanently stopped at the discretion of the investigator.

Any patient with grade 4 renal, hepatic, cardiac or hematological toxicity will be immediately discontinued from study therapy. The laboratory test or clinical finding in question will be reassessed as soon as possible. The repeat test will guide management of the event as follows:

- If the repeat assessment shows toxicity of grade 3 or lower, and if the patient has continued to receive study drugs between the two testing dates, then the patient will be managed according to the appropriate toxicity level of the repeat test.
- If the repeat test shows toxicity of grade 3 or lower, and if the patient has not received study drugs between the two testing dates, then the patient will be managed at the discretion of the investigator with regard to the re-administration of study drugs, and otherwise according to the toxicity level of the repeat test.
- If the repeat test shows grade 4 toxicity, then the patient will be permanently discontinued from study medications. Further treatment of TB will be directed by the investigator on an individualized basis. The patient will continue to be followed for study monitoring purposes (as are other patients who make a permanent departure).

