| Conductive hearing loss is graded as Middle ear/hearing in the AUDITORY/HEARING category. | | | | | |
| Earache is graded in the PAIN category. | | | | | |
| External auditory canal | normal | external otitis  with erythema or  dry desquamation | external otitis  with moist  desquamation | external otitis  with discharge,  mastoiditis | necrosis of the  canal soft tissue  or bone |
| Note: Changes associated with radiation to external ear (pinnae) are graded under Radiation dermatitis in the DERMATOLOGY/SKIN category. | | | | | |
| Inner ear/hearing | normal | hearing loss on  audiometry only | tinnitus or  hearing loss,  not requiring  hearing aid or  treatment | tinnitus or  hearing loss,  correctable with  hearing aid or  treatment | severe unilateral  or bilateral  hearing loss  (deafness), not  correctable |
| Middle ear/hearing | normal | serous otitis  without subjective  decrease in  hearing | serous otitis or  infection  requiring  medical  ntervention; subjective  decrease in  hearing;  rupture of  tympanic  membrane with  discharge | otitis with  discharge,  mastoiditis or  conductive  hearing loss | necrosis of the  canal soft tissue  or bone |

| Auditory/Hearing  Other  (Specify,__________) | normal | mild | moderate | severe | severe life  threatening or  disabling |
| --- | --- | --- | --- | --- | --- |
| **BLOOD/BONE MARROW** | | | | | |
| Bone marrow cellularity | normal for age | mildly  hypocellular or  25% reduction  from normal  cellularity for  age | moderately  hypocellular  or >25 - <50%  reduction from  normal  cellularity for age or >2  but <4 weeks to  recovery of  normal  bone marrow cellularity | severely  hypocellular or  >50 - <75%  reduction  in cellularity for  age or 4 - 6  weeks to  recovery  of normal bone marrow cellularity | aplasia or >6  weeks to  recovery of  normal  bone marrow  cellularity |
| CD4 count | WNL | <LLN - 500/mm 3 | 200- <500/mm 3 | 50 - <200/mm 3 | <50/mm 3 |
| Hemoglobin (Hgb) | WNL | <LLN - 10.0 g/dL  <LLN - 100 g/L  <LLN - 6.2 mmol/L | 8.0-<10.0 g/dl  80 - <100 g/L  4.9 - <6.2 mmol/L | 6.5 - <8.0 g/dL  65 - <80 g/L  4.0 - <4.9 mmol/L | <6.5 g/dL  <65 g/L  <4.0 mmol/L |
| Leukocytes (total WBC) | WNL | <LLN- 3.0x10 9 /L  <LLN- 3000/mm3 | >2-<3.0x10 9 /L  >2000 -  <3000/mm 3 | >1.0 - <2.0 x  109 /L  >1000 -  <2000/mm 3 | <1.0 x 10 9 /L  <1000/mm 3 |

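### Laboratory grading takes no account of the screening value and includes CD4 count, so low CD4 or anaemia that predates treatment can count as Grade 3/4 toxicity, with CD4 affecting HIV-infected patients only

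*Protocol*

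**What the plan says.** **Grading.** Protocol Section 5.3 (Study drug toxicity): "All symptoms and laboratory findings will be graded according to severity using the modified National Cancer Institute Common Toxicity Criteria (Appendix E". Nothing in that sentence refers to the value at screening.

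**CD4 and haemoglobin bands.** In Appendix E, under Blood/Bone Marrow, the CD4 row begins "CD4 count | WNL | <LLN - 500/mm 3" and its Grade 3 and Grade 4 cells read "50 - <200/mm 3 | <50/mm 3". In the same block haemoglobin is Grade 3 from 6.5 to <8.0 g/dL and Grade 4 below 6.5.

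**When CD4 is measured.** Section 4.1.3 says that patients found to be HIV-infected at screening "will have blood drawn for a CD4 cell count at the week 2 study visit", or at the first visit after HIV is documented. The same applies to known HIV-infected patients with no written result from the preceding six months. Section 5.11 and note 6 of Appendix D repeat this.

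**Entry.** Section 3.8.1 requires "Complete blood count with hemoglobin level of at least 7.0 g/dL". It sets no CD4 limit.

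**Consequences of a grade.** Section 5.4 makes Grade 3 or 4 toxicity reportable whatever its cause and treats every Grade 4 toxicity as a serious adverse event. Section 5.5 states: "Any patient with grade 4 renal, hepatic, cardiac or hematological toxicity will be immediately discontinued from study therapy". The stop becomes permanent if the repeat test is still Grade 4.

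**Where the grades are used.** Section 3.4 includes an adverse-event comparison of HIV-infected with uninfected patients. Section 3.5 makes Grade 3 and 4 toxicities a secondary safety endpoint, and discontinuation of the assigned regimen for any reason the main safety and tolerability endpoint.

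**The concern.** A toxicity endpoint should record what happens after treatment starts. Here two laboratory items can be Grade 3 or worse because of the patient's state on arrival.

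CD4 matters more. Only HIV-infected patients have it drawn, and its first value may come two weeks into treatment. A low count that reflects HIV disease then looks like an on-treatment finding. Uninfected patients cannot have such an event because they never have the test. Even within the HIV-infected group, two patients with the same CD4 count are handled differently depending on whether a recent result was already on file.

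A literal reading also reaches patient management. A first CD4 below 50 would be a serious adverse event and would meet the discontinuation rule. A resulting stop would count in the discontinuation endpoint. If it led to more than 14 days of non-study therapy in the intensive phase, Section 6.1 would remove the patient from the culture-conversion analysis.

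For haemoglobin the issue is smaller: a patient admitted at 7.5 g/dL who stays at 7.5 g/dL shows a Grade 3 value at every visit.

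**Working it through.** The protocol gives no figure of its own on this point, so there is none to reproduce. The check has three steps.

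**1. Place each entry limit in the Appendix E bands.**

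| Test | Entry limit (3.8.1) | Relevant bands (Appendix E) | Grade at the limit |
|---|---|---|---|
| Haemoglobin | ≥7.0 g/dL | Grade 3: 6.5 to <8.0; Grade 4: <6.5 | 3 |
| Platelets | ≥50,000/mm³ | Grade 2: 50,000 to <75,000; Grade 3: below 50,000 | 2 |
| AST | ≤3 × ULN | Grade 2: >2.5 to 5.0; Grade 3: >5.0 | 2 |
| Bilirubin | ≤2.5 × ULN | Grade 2: >1.5 to 3.0; Grade 3: >3.0 | 2 |
| Creatinine | ≤2 × ULN | Grade 2: >1.5 to 3.0; Grade 3: >3.0 | 2 |
| CD4 | none | Grade 3: 50 to <200; Grade 4: <50 | any |

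The platelet boundary is read as inclusive. Among tests with an entry limit, only haemoglobin can be Grade 3 at entry (7.0 to <8.0), and none can be Grade 4. The lowest eligible haemoglobin must fall by more than 7.0 − 6.5 = 0.5 g/dL to become Grade 4. CD4 alone can be Grade 4 with no change on treatment.

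**2. HIV comparison, by illustration.** Assume the same emergent Grade 3/4 rate, 10%, in both groups. Let s be the share of all HIV-infected patients with an on-treatment CD4 below 200. The recorded rate in HIV-infected patients is s + (1 − s) × 0.10, assuming independence:

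- s = 0.20: 0.20 + 0.80 × 0.10 = 28%
- s = 0.40: 0.40 + 0.60 × 0.10 = 46%
- s = 0.60: 0.60 + 0.40 × 0.10 = 64%

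The uninfected rate stays at 10%. The whole difference comes from the CD4 test.

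**3. Comparison between arms, by illustration.** Assume emergent rates of 10% and 20%, with 205 patients per arm (Section 3.7). Let a share q of each arm count as Grade 3/4 because of baseline state. The recorded rates are q + (1 − q) × 0.10 and q + (1 − q) × 0.20. Power is for a two-sided 5% comparison of two proportions.

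| q | Recorded rates | Risk ratio | Difference | Power |
|---|---|---|---|---|
| 0 | 10% v 20% | 2.00 | 10.0 points | 81% |
| 5% | 14.5% v 24% | 1.66 | 9.5 points | 69% |
| 10% | 19% v 28% | 1.47 | 9.0 points | 58% |
| 20% | 28% v 36% | 1.29 | 8.0 points | 41% |

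Randomisation should balance q between arms, so the contrast shrinks but is not pushed towards either regimen.

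The values of s, q and the emergent rates are assumptions. The protocol says only that many enrolled patients will have HIV. It gives no HIV share, no CD4 distribution and no frequency of haemoglobin between 7.0 and 8.0.

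**The case against.** The best case against is that the protocol does not intend CD4 as a toxicity test. Section 4.1.3 names the toxicity-monitoring tests as blood count, AST, bilirubin and creatinine, and ties CD4 to referral for HIV care. Appendix E is a general oncology dictionary that also grades tumour pain. Sections 5.3 and 5.6 speak of treatment-emergent toxicity. Section 5.4 makes a pre-existing diagnosis reportable when its signs or symptoms worsen to Grade 3 or 4. In Section 5.5 the Grade 3 hold depends on the investigator's attribution to study drug. Finally, deriving treatment-emergent grades is commonly left to an analysis plan, which is not shown.

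Much of this stands. It shows that the intention was probably narrower than the wording, and the absence of a detailed derivation is not the fault raised here. But Section 5.3 covers all laboratory findings, and CD4 is one with its own row. None of the softer wording is attached to the Grade 3/4 endpoint or to the Grade 4 rule in Section 5.5, which carries no condition on cause or baseline. Sites report and stop treatment under the protocol, and a later analysis plan cannot undo that.

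Stronger readings are tempting but unsupported:

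- A reader might infer that all laboratory grading is affected. Eligible platelet, AST, bilirubin and creatinine values are at most Grade 2.
- A reader might infer that HIV status itself is graded. Only a CD4 below 200 reaches Grade 3 or 4.
- A reader might infer that baseline anaemia triggers discontinuation. It is Grade 3 at most, and admitting such patients does not contradict the Grade 4 rule.
- The rule in Section 5.5 concerns the individual patient and is not a trial stopping rule.
- Table 6 (17.2% with any reportable event) is not a usable yardstick. It comes from a trial in HIV-infected patients and counts any reportable event, not Grade 3/4.

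**Conclusion.** The point holds for two items. CD4 grading gives HIV-infected patients a route to a Grade 3/4 event that uninfected patients do not have, which directly biases one secondary, non-randomised comparison. Unchanged haemoglobin of 7.0 to <8.0 g/dL can count in the Grade 3/4 endpoint; between randomised arms this dilutes the contrast without favouring either regimen.

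The protocol also conflicts with itself on CD4. Read literally, Sections 5.3 to 5.5 and Appendix E make a first CD4 below 50 a serious adverse event and a reason for discontinuation, while Section 4.1.3 and the treatment-emergent and worsening wording point away from that. Whether any patient would be stopped on this ground, and how many would be counted as Grade 3/4, cannot be derived from the protocol. The illustrative rates show direction and sensitivity only. The change is worth making because it costs little, but the culture-conversion comparison is touched only if CD4-driven stops actually occur.

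**What to change.** In Sections 3.5 and 6.1, for the Grade 3/4 safety endpoint and the HIV comparison, count a laboratory Grade 3 or 4 only when it is at least one grade worse than the screening value. Leave CD4 count out of both by name. The worsening rule alone would not deal with CD4, because patients drawn at week 2 are those without a recent result to compare with.

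The cost is a sentence or two in those sections and a note to Appendix E. Section 4.1.1 already provides a blood count, AST, bilirubin and creatinine at screening or within the previous 14 days, so no new data are needed. The small downside is that a further fall within Grade 3, in a patient who starts at Grade 3, is not counted; a fall to Grade 4 still is.

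Sections 4.1.3, 5.3, 5.4, 5.5 and 5.6 and the CD4 row of Appendix E must be reconciled by the clinical team. No clinical rule is proposed here.
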